## Abstract

**Background:**

Enhanced Recovery After Surgery (ERAS) programmes aim at an early recovery after surgical trauma and consequently at a reduced length of hospitalisation. This paper presents the protocol for a study that focuses on large-scale implementation of the ERAS programme in major gynaecological surgery in the Netherlands. The trial will evaluate effectiveness and costs of a stepped implementation approach that is characterised by tailoring the intensity of implementation activities to the needs of organisations and local barriers for change, in comparison with the generic breakthrough strategy that is usually applied in large-scale improvement projects in the Netherlands.

**Methods:**

All Dutch hospitals authorised to perform major abdominal surgery in gynaecological oncology patients are eligible for inclusion in this cluster randomised controlled trial. The hospitals that already fully implemented the ERAS programme in their local perioperative management or those who predominantly admit gynaecological surgery patients to an external hospital replacement care facility will be excluded. Cluster randomisation will be applied at the hospital level and will be stratified based on tertiary status. Hospitals will be randomly assigned to the stepped implementation strategy or the breakthrough strategy. The control group will receive the traditional breakthrough strategy with three educational sessions and the use of plan-do-study-act cycles for planning and executing local improvement activities. The intervention group will receive an innovative stepped strategy comprising four levels of intensity of support. Implementation starts with generic low-cost activities and may build up to the highest level of tailored and labour-intensive activities. The decision for a stepwise increase in intensive support will be based on the success of implementation so far. Both implementation strategies will be completed within 1 year and evaluated on effect, process, and cost-effectiveness. The primary outcome is length of postoperative hospital stay. Additional outcome measures are length of recovery, guideline adherence, and mean implementation costs per patient.

**Discussion:**

This study takes up the challenge to evaluate an efficient strategy for large-scale implementation. Comparing effectiveness and costs of two different approaches, this study will help to define a preferred strategy for nationwide dissemination of best practices.

**Trial registration:**

Dutch Trial Register NTR4058

## Background

Malignant neoplasms are the most important indication for major surgery in gynaecology in the Netherlands each year. Approximately 2500 women undergo gynaecological surgery for ovarian, endometrial, or cervical cancer. In the last decades, several efforts have been made in trying to reach optimal perioperative management. In the late 1990s, Kehlet introduced a renewal process aiming to maintain normal physiology after surgery [1]. Several evidence-based elements were combined in a perioperative management programme, designed to enhance recovery from major surgical trauma [2]. The Enhanced Recovery After Surgery (ERAS) programme proved to be safe with favourable effects on recovery and length of stay [3–6]. Although this programme has been successfully implemented in elective colonic surgery, a spontaneous diffusion of the ERAS programme in other elective surgery areas did not occur [7–11]. Patients undergoing major surgical procedures remain subjected to unpleasant, unnecessary, and harmful practices, despite of a large body of evidence supporting perioperative management improvements [12–14]. As a result, patients are exposed to an unnecessary prolonged hospital stay. Efficient implementation of the ERAS programme in elective gynaecological surgery on a large scale is challenging.

In 2010, the ERAS programme was successfully introduced in major gynaecological surgery at the Department of Gynaecology of Maastricht University Medical Centre [11]. This resulted in a significant reduction in length of hospital stay. Nationwide implementation of the ERAS programme in elective gynaecological surgery did not happen yet, while this is necessary to achieve high standards of care and evidence-based practice, with subsequent benefits for the successful execution of clinical trials within this field [15, 16]. Further, reduced hospitalisation will save costs and will facilitate the increased patient load by the imminent centralisation of major gynaecological surgery in the assigned high-volume centres in the Netherlands. Finally, a reduced functional decline after surgery will ease the required early start of postoperative adjuvant chemotherapy in patients with ovarian cancer.

In the Netherlands, the quality improvement model known as the Breakthrough Series [17] is currently adopted as the preferred method for health care improvement on a large scale, despite some serious drawbacks [18]. This structured collaborative learning strategy is designed to help health care organisations attain best practice in a certain field. Systematic evaluations have shown that effectiveness of the breakthrough approach varies and is at the best moderate [19]. Furthermore, breakthrough projects represent substantial investments of time, effort, and funding and are assumed to be expensive [20]. A new approach designed to deliver an optimal effect of implementation efforts at the lowest possible implementation costs is desirable. Based on the underlying assumption that organisations may vary widely in their knowledge, motivation, and capacity to run a quality improvement programme, as prescribed in the meta-evaluation of ten such programmes in the Netherlands [21], a stepped implementation strategy was designed. This strategy aims to tailor the implementation efforts to the variety in needs and local barriers to change. It offers generic low-intensive support for those who smoothly implement the changes and a more tailored and intensive approach for those hospitals having difficulties in making the changes. This differentiation of the implementation activities to preparedness for change is described in various theories on the different phases in a process of change. The Model for Planning Change of Grol describes ten stages, subdivided into awareness, understanding, acceptance, adoption, and integration of the proposed behaviour [22, 23]. This model was used to select the change interventions that will be used in the stepped implementation strategy. Each step leads to a more intensive stage in the process of change. A tailored approach is intensive and seems less suitable for large-scale improvement as it requires local support and elaborative preparatory activities [24, 25]. Evaluation of the process of this implementation effort will provide insight on why and for whom the developed strategy works and improves the understanding of the stepped approach. This will help to define a preferred strategy for nationwide dissemination of best practices.

### Objectives

The objective of this study is to compare effectiveness and costs of a stepped implementation strategy versus the generic traditional breakthrough methodology for the nationwide uptake of the ERAS approach. In addition, the current study aims to identify intervention fidelity and contextual factors that influence implementation by means of a process evaluation. The overall aim is to define a preferred strategy for the large-scale implementation of evidence-based practice. This paper describes the study protocol.

## Methods

### Design

The present study is a non-blinded cluster randomised controlled trial with two arms comparing an innovative stepwise implementation approach to the existing generic breakthrough approach. After approval to participate, a retrospective baseline measurement of 30 patients will be performed to assess current perioperative practice. Cluster randomisation will be applied at the hospital level and will take place after all retrospective measurements have been completed. Randomisation will be executed at the central level by an independent statistician of Maastricht University. The hospitals will be allocated to the intervention (stepped strategy) or to the control group (breakthrough strategy) (Fig. 1). After 1 year, the implementation process will be ended by a final sustainability meeting for both groups. We assume differences in uptake of innovations between the high-volume tertiary care hospitals and their affiliated regional hospitals. Stratified randomisation will be used to prevent unbalanced intervention groups with respect to tertiary status or not.

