### Data collection

Before the start of implementation activities, a baseline audit of process and outcome data will be performed by reviewing medical charts of the first 30 patients treated in 2012. This period was chosen as the ERAS programme was not discussed yet in the DGOG. In case of an insufficient number of patients, the retrospective audit will be completed with patients operated in 2011. Hereafter, from the first day of the start till the end of the project 1 year later, a member of the expert team will monitor process and outcome data for both the intervention and the control group. An electronic database supporting good clinical practice guidelines will be available. Patient characteristics, process indicators, and outcome measures (proportion of patients reaching functional recovery within 3 days and proportion of patients hospitalised for a maximum of 5 days) will be audited for every 3-month period during the 1-year implementation period. The timing of the teaching sessions of the breakthrough project will be synchronous with the timing of the implementation steps (Fig. 2). Although the effectiveness of both strategies will be evaluated and compared every 3 months after every step or teaching session, the main goal of the study is to compare effectiveness at the end of the project using all patients collected during the year. Costs for the two implementation strategies will be calculated from hours and tariffs for the strategy delivery team (CBO expert, subject matter experts) as well as all costs for surgeons, anaesthetists, and nurses attending implementation-related activities, including time, travel, and conference expenses. Furthermore, the costs of materials will be calculated. Additional costs of the audit database will be calculated as well, as this is an essential part of the implementation strategies. Standardised forms will be developed for the measurement of activities, materials, and expenses associated with implementation [34]. Those forms will be filled in by members of the implementation team at each site and will provide information for the economic and process evaluation of the quality mprovement. Qualitative data regarding the process evaluation will be derived from extensive notes of all contacts with each hospital and during the educational sessions. Minutes will be taken by at least two members of the expert or local implementation team.

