### Sample size

With the support of the DGOG, we expect to include the majority of Dutch hospitals and all patients that will be exposed to major gynaecological surgery during the implementation year. Approximately 100 patients undergo surgery per hospital per year. We do not expect drop outs among patients as informed consent procedures and filling in questionnaires by patients is not needed. The history of adherence to the ERAS protocol in the Netherlands during the implementation year will be described, so this study is in principle not about statistics and sample size calculations. However, it may be still worthwhile to calculate what statistical differences we will be able to assess, taking the perspective that this sample can be seen as an estimate for the future health care or assuming that some hospitals will not participate as expected. The stepped implementation strategy is expected to be superior to the breakthrough strategy in improving perioperative care processes and reducing the length of hospital stay. Anticipating a total adherence of 50 % to the benchmark of length of stay of 5 days or less in the breakthrough hospitals versus 70 % adherence in the stepped implementation hospitals, we would need to randomise seven hospitals per arm, each including at least 60 patients during the whole study period. Sample size computation was based on an estimated intra-class correlation coefficient (ICC) of 0.06 in secondary care, a power level of 80 %, and a significance level (*α*) of 0.05. The intra-class correlation coefficient used to calculate the sample size was based on a study of Campbell et al. [35]. Although this study reported significantly lower ICCs for outcome variables compared to process variables, we have conservatively computed the sample size using the highest applicable ICC of 0.06 for secondary care. Using an inflation factor of 11 % to account for unequal cluster size yields a recruitment target of 67 patients per cluster. It is possible that no clinically relevant differences (<20 %) between arms could be found. In such a case, we expect the stepped implementation programme still to be superior from a financial perspective.

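### The completed baseline audits are used neither to balance the single allocation of about 14 hospitals nor, in the stated model, as a covariate: an avoidable loss of precision, not a bias

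*Protocol article*

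**What the plan says.** All quotations are from the protocol article.

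- **Design.** Allocation is central: "Randomisation will be executed at the central level by an independent statistician of Maastricht University". It "will take place after all retrospective measurements have been completed". The one balancing factor is tertiary status: "Stratified randomisation will be used to prevent unbalanced intervention groups with respect to tertiary status or not". The reason given is "We assume differences in uptake of innovations between the high-volume tertiary care hospitals and their affiliated regional hospitals".
- **Data collection.** Before any implementation activity, "a baseline audit of process and outcome data will be performed by reviewing medical charts of the first 30 patients treated in 2012", topped up with 2011 patients where needed.
- **Participants (Hospitals).** The audit also decides whether a hospital is excluded because it already runs the full programme, so it has to be read before allocation.
- **Sample size.** "we would need to randomise seven hospitals per arm, each including at least 60 patients during the whole study period", for 50 % against 70 % with a stay of 5 days or less, ICC 0.06, 80 % power and alpha 0.05. The ICC is described as conservative because outcome variables had lower values. On volume the section gives "Approximately 100 patients undergo surgery per hospital per year" and "Using an inflation factor of 11 % to account for unequal cluster size", but no spread between hospitals.
- **Data analysis (Effect evaluation).** The model has a random hospital effect and the implementation period as a factor. No baseline hospital value is named.

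**The concern.** With about seven hospitals per arm, stratifying on one binary factor leaves the arms' starting level of stay, and much of their volume, to chance. The data needed to limit that chance are in hand when the statistician draws the allocation, and the same data could sharpen the analysis. As described, the plan does neither.

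Three things are at stake.

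1. Precision of the arm comparison, which has 80 % power with nothing to spare at seven hospitals per arm.
2. Face validity. A visible baseline gap in a non-blinded trial of a few hospitals is hard to explain away afterwards.
3. The cost comparison. Meeting and expert costs accrue largely per hospital or per session, so patient volume is the denominator of cost per patient. At equal spending, an arm with 25 % more patients has a cost per patient of 1/1.25 = 0.80 times the other's. The stepping rule also depends on the share of patients home within 5 days, so an intervention arm that starts higher by chance may step up less and look cheaper.

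**Working it through.** **1. The plan's own figure.** For 50 % against 70 %, two-sided 0.05 and 80 % power, the two-proportion formula gives 93 patients per arm. The design effect is 1 + 59 × 0.06 = 4.54. Then 93 × 4.54 = 422 per arm, and 422/60 = 7.04 hospitals. With 7 × 60 = 420 per arm, power is 79.8 %. Finally 60 × 1.11 = 66.6, rounded to 67. The stated sample size reproduces.

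**2. Chance imbalance in true level under stratified allocation.** At a 50 % rate the between-hospital variance is ICC × 0.25. With seven hospitals per arm, the SD of the difference in arm means is √(2 × ICC × 0.25 / 7), if tertiary status explains none of that variance.

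| ICC | SD of difference | Chance of a gap of 10 points or more |
|---|---|---|
| 0.06 | 6.5 points | 12.7 % |
| 0.02 | 3.8 points | 0.8 % |

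Simulation over all stratified 7:7 allocations, with assumed tertiary/regional splits of 6/8 (1,400 allocations) and 4/10 (1,512), gives 12-13 % at ICC 0.06. With an assumed baseline rate of 30 %, and with tertiary status explaining 0 or 30 % of the hospital variance, the range is about 4-9 %.

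**3. How well the audit measures the true level.** The reliability of 30 charts is ICC / (ICC + (1 − ICC)/30). This is 0.06/(0.06 + 0.0313) = 0.66 at ICC 0.06, and 0.02/(0.02 + 0.0327) = 0.38 at ICC 0.02.

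**4. What constrained allocation would do.** In the simulation (30 % baseline rate, ICC 0.06), a random draw from the best-balanced 10 % of stratified allocations cuts the SD of the *audited* gap from 6.4-7.5 to 1.6-1.8 points, about 94 % of its variance. The variance of the *true* gap in the trial year falls by about c² × reliability × 0.94, where c is the assumed correlation between a hospital's true level in the audit year and in the trial year. At ICC 0.06 and a 50 % rate:

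| c | Remaining variance | SD | Chance of a gap of 10 points or more |
|---|---|---|---|
| 0.5 | 0.85 | 6.0 points | 9.7 % |
| 0.7 | 0.70 | 5.5 points | 6.7 % |
| 1.0 | 0.38 | 4.0 points | 1.3 % |

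Simulation agrees: about 9-10 %, 6-7 % and 1 %.

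**5. What adjustment would do.** Adjusting for the audited value leaves a residual ICC of ICC × (1 − c² × reliability). Estimating one covariate from 14 hospitals, after intercept and stratum (12 degrees of freedom), costs an expected factor of 10/9 = 1.11 under stratified allocation and about 1.01 under constrained allocation. Variance of the arm effect relative to no adjustment, at 60 patients per hospital:

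| ICC | c | Design-effect ratio | Adjustment only (× 1.11) | Constrained and adjusted (× 1.01) |
|---|---|---|---|---|
| 0.06 | 0.5 | 3.96/4.54 = 0.87 | 0.97 | 0.88 |
| 0.06 | 0.7 | 3.40/4.54 = 0.75 | 0.83 | 0.76 |
| 0.02 | 0.5 | 2.07/2.18 = 0.95 | 1.05 | 0.96 |
| 0.02 | 0.7 | 1.96/2.18 = 0.90 | 1.00 | 0.91 |

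**6. Volume.** The spread is not in the documents. With an assumed CV of 0.5, unrelated to tertiary status, arm totals differ by 25 % or more in about 39 % of stratified allocations, against under 1 % when constrained. For CVs of 0.37 to 0.78, two readings of the plan's 11 % allowance, the ranges are about 25-58 % and 0-7 %. They would be lower to the extent that tertiary status captures volume.

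**The case against.** The plan contains no error or contradiction here. Stratified allocation by an independent statistician is sound, the choice of stratum is justified, and chance variation between hospitals is what the ICC pays for. A reader might infer that the trial is biased or the sample size wrong. Neither follows: the size reproduces, and randomisation protects the comparison.

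A reader might also infer that large imbalance is likely and that constrained allocation would remove most of it. The documents do not support that. A 10-point gap is a tail event even at the ICC the plan calls its highest applicable value. Seven per arm is a calculated minimum: 2,500 women a year (Background) at about 100 per hospital suggests up to 25 hospitals, and with 12 per arm the chance at ICC 0.06 is about 4.5 %. The charts date from 2012 or 2011 and are few, so only the audited gap nearly vanishes.

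The volume figures rest on an assumed spread, and the protocol does not say that annual volumes are known at allocation. A separate analysis plan may specify adjustment, and a condensed article that omits cost adjustment is not at fault for that. The Trial status section reports the last phase of implementation, so allocation is presumably done.

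All of this stands, and it limits the size and urgency of the point. It leaves the fact that data in hand could improve precision at almost no cost.

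**Conclusion.** The point holds as an efficiency and credibility improvement. The baseline audits precede one central allocation, yet they are used neither in that allocation nor in the stated model. At ICC 0.06, a 50 % rate and seven hospitals per arm, constraint would lower the chance of a true 10-point gap from about 12-13 % to about 6-10 % for correlations of 0.5-0.7. At a correlation of 0.7, adjustment alone cuts the variance of the effect by about 17 %, and constraint plus adjustment by about 25 %. At ICC 0.02 such a gap is rare under either scheme, and adjustment alone gains little or nothing unless hospital levels persist strongly. The baseline-to-trial correlation, the strata sizes and the volume spread are assumptions. The documents give none of them.

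**What to change.** - **If allocation is still open:** within the tertiary strata, list all allocations, score each on the arm difference in audited baseline stay (or 5-day proportion) and, where available, annual volume, and draw one at random from the best-balanced 10-20 %. This takes one program run by the independent statistician, with no new data or patients.
- **In either case:** add the hospital's audited baseline value and the tertiary stratum to the mixed model under Data analysis (Effect evaluation). Report baseline stay and volume by arm. Show the net-cost comparison also standardised for baseline stay and volume, beside the unstandardised one. If a separate analysis plan already does this, a sentence pointing to it is enough.

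The cost is one or two degrees of freedom at hospital level. If the ICC is low or the baseline-to-trial correlation weak, the gain is small or nil, and adjustment alone can lose a few per cent of precision (factor 1.05 at ICC 0.02 and correlation 0.5). The covariates should therefore be fixed before the outcome data are compared by arm.

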**Fig. 1 Fig1:**
[figure not shown]
Flowchart SINERGY trial

### Participants

#### Hospitals

All Dutch Gynaecology Oncology Group (DGOG) tertiary referral hospitals and their affiliated regional hospitals authorised to perform major gynaecological surgery will be invited to participate in this implementation study. The authorisation is based on the volume norm set by the Dutch Association of Gynaecologists in 2013. The hospitals that already fully implemented the ERAS programme in their local perioperative management are not eligible to participate. Exclusion will be based on findings of the baseline audit. To avoid interference in outcome measures, the hospitals that predominantly admit gynaecological surgery patients to an external hospital replacement care facility after discharge will be excluded as well. The DGOG, a national collaborative of professionals involved in the treatment of women with gynaecological cancers that aims to promote (inter)national research in gynaecological cancer, supports the underlying aim to reach nationwide standardisation of perioperative care consistent with the ERAS programme. This will support the recruitment of eligible hospitals in the study. In addition, we expect that cancellation of the usual 20,000 euro fee for participation to a Dutch Institute for Healthcare Improvements (CBO)-guided breakthrough project will be an important incentive towards participation. For all participating hospitals, costs of implementation are brought back to costs of joining meetings and costs of executing local activities.

